### Randomization procedure and blinding

After the baseline assessment, participants are randomized to either ACTonHEART or usual care with the condition assignment determined via a computer generated algorithm. A block randomization scheme is employed, balancing gender and baseline impact of modifiable cardiovascular risk factors assessed using the INTERHEART Modifiable Risk Score (highest tertile vs. middle tertile). Participants allocated to the ACT condition are then scheduled into treatment groups. Randomization and follow-up assessments will be administered by independent practitioners blind to condition assignment and research hypotheses.

### Statistical analysis

Preliminary analyses will be conducted to test parametric statistical assumptions. If strong violations are detected, robust methods or data transformation will be applied. Outcome measures will be examined with intention-to treat analyses and analyses will be conducted on treatment completers.

Since participants in the ACT condition will be clustered into small therapy groups, the between-group variance should be taken into account. In fact, it has been shown that ignoring this level of nesting in the data can affect estimated variances and power to detect treatment and covariate effects [73], significantly inflate the Type I error rate and treatment effect size [74]. Thus, given the partially-nested design of this study, data will be analysed according to the guidelines suggested by Daniel J. Bauer and colleagues in their seminal paper [75]. Two-tailed tests with an adjusted critical alpha of 0.01 (0.05/4) will be conducted for examining the treatment effects on the four primary outcomes. Furthermore, on the basis of the best multilevel model structured in the primary analyses, the moderating effects of some putative covariates such as gender, age, level of education, marital status, cardiovascular disease status, and diabetes, will be explored and no adjustment to alpha will be applied. Beyond these analyses we also intend to explore the effects of ACT on measures of dietary habits and physical activity, smoking cessation, medication adherence and health-related quality of life, exercise capability during an incremental bicycle stress test, lipid profile, glycosylated haemoglobin level, and waist to hip ratio. The mediating role of psychological inflexibility will also be examined within the structured multilevel model. The MLwiN 2.21 sofware (Centre for Multilevel Modeling-CMM, University of Bristol) will be used for data analysis.

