#### Study objectives and hypotheses

To the best of our knowledge this will be the first randomized controlled trial to evaluate the efficacy of ACT in cardiac patients. Thus, the main aim of this research is to examine the efficacy of a manualized ACT-group therapy program for preventing the long-term deterioration of several risk factors and lifestyle behaviors and for improving psychological well-being and quality of life in patients with IHD over a 12-months follow-up period. In order to reflect Medical Research Council recommended guidelines [50] as well as the multi-factorial nature of the intervention, a number of primary outcome measures will be considered.

Moreover, the study is aimed at exploring the mechanisms of change surrounding the intervention with increased psychological flexibility as a possible critical mediator of intervention effects.

Specifically, the current study is designed to test the following hypotheses:

Primary hypothesis: The proposed ACT intervention will be associated with significantly better achievement, compared to the usual care, in at least two of the following primary outcome measures: LDL-cholesterol, resting systolic blood pressure, body mass index, and psychological well-being measured by the Psychological General Well-Being (PGWB) Index.

As no RCT was available on ACT-based interventions for cardiac patients, at the time of the study design we were not able to predict the modification of these four outcome variables as effect of the intervention.

Otherwise, expected levels of change on some of these indicators can be projected for participants in the usual care condition based on the GOSPEL study [51], a recent Italian survey on a similar population. Results from this study showed time-related worsening of the management of cardiac risk factors at 12-months follow-up. In particular, in the usual care condition, the following mean changes from baseline to 12-months follow-up were observed: an increase of 0.4 mg/dl in LDL cholesterol levels, an increase of 0.4 Kg/m^2^ in BMI and a 15.2% decrease in the rate of patients at target for resting systolic blood pressure [51].

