### Sample size

The primary outcome variables of this study are the mean changes on the following indicators: LDL-cholesterol, resting systolic blood pressure, body mass index, and psychological well-being measured by the PGW.

As outlined above, at the time of the study’s design, we were unable to project the level of improvement on these outcome measures as effect of the ACT intervention over a 12 months follow-up period, since no data on cardiac patients were available.

Hypothesizing a medium effect size of the ACT intervention (in particular a standardized effect of at least 0.3 standard deviations) the following between-group differences on mean changes from baseline to 12-month follow-up are expected: 8.8 mg/dl in LDL cholesterol, 4 mmHg on systolic resting blood pressure and 1.3 kg/m^2^ in BMI. According to general guidelines, a power level of .80 is considered adequate to detect treatment effects [71]. In accordance with deJong and colleagues [72], a clustered design will require 160 participants to detect medium treatment effects with a statistical power of 0.8 and a significance level of .05.

Assuming a drop-out rate of <5% (as found in the GOSPEL study [51]), a sample size of 168 participants was finally defined, resulting in 84 participants being randomly assigned to each group.

Data on “lost to follow-up” participants will be analyzed to identify any relevant characteristics that may differ from the remainder of the study group. All data for the primary and secondary outcome measures will be analyzed using an intention-to-treat analysis such that participants will remain in their randomly assigned groups at final analysis, regardless of actual participation within such group.

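### The critical alpha for the four primary outcomes is printed as 0.01, but the division beside it gives 0.0125, and the two-of-four primary hypothesis can turn on the difference

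*Protocol article*

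**What the plan says.** The Statistical analysis section of the protocol article specifies two-sided tests at an "adjusted critical alpha of 0.01 (0.05/4") and says that these tests "will be conducted for examining the treatment effects on the four primary outcomes". The same sentence thus gives the threshold as a figure and as a formula.

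Study objectives and hypotheses defines success differently: ACT must do significantly better than usual care "in at least two of the following primary outcome measures", namely LDL-cholesterol, resting systolic blood pressure, BMI and the PGWB index. The analysis section does not say how its threshold feeds that rule.

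The Sample size section assumes "in particular a standardized effect of at least 0.3 standard deviations" and arrives at 160 participants before drop-out.

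**The concern.** The threshold is the decision rule for every primary outcome, and it is written as two numbers that disagree. An outcome with p = 0.011, for example, fails by the printed figure and passes by the printed division. If exactly one other outcome has clearly passed, the primary hypothesis is met under one reading and not under the other. A prespecified threshold exists so that this choice cannot be made once the p-values are known. Nothing else in the article settles which number governs. An analysis plan that is not shown does not remove the problem, because the article itself prints the conflicting figure.

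**Working it through.** **Inputs.** From the article: overall alpha 0.05, four primary outcomes and two-tailed tests (Statistical analysis); success on at least two of four (Study objectives and hypotheses); 0.3 SD and 160 participants, so 80 per arm (Sample size); therapy groups of 8 (The ACTonHEART intervention). Assumed, because the article gives neither: an intraclass correlation (ICC) in the ACT arm of 0 to 0.10, and an equal correlation r between outcomes of 0 to 0.6.

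**1. Reproducing the printed figure.**
- Bonferroni: 0.05/4 = 0.0125, not 0.01.
- Šidák: 1 − 0.95^(1/4) = 0.0127.
- 0.05/5 = 0.01, but four outcomes are named, not five.
- 0.04/4 = 0.01, but the overall level shown is 0.05.
- Rounding 0.0125 to two decimals gives 0.01, but the text does not say that the figure is rounded.

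**2. Chance of any false positive among the four tests** (bound 4α; if independent, 1 − (1 − α)^4).
- α = 0.01: bound 0.040; independent 0.0394.
- α = 0.0125: bound 0.050; independent 0.0491.

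**3. Chance of a false two-of-four claim.** The worst case is one outcome truly improved and certain to be significant, with three null. The claim is then false if any of the three nulls is rejected, so the bound is 3α.
- α = 0.01: 0.030.
- α = 0.0125: 0.0375.
- α = 0.05/3 = 0.0167: 0.050.
- α = 0.025: 0.075, which would not be acceptable.

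**4. Power at 0.3 SD.** The standardized test statistic has mean 0.3 / √[(1 + 1 + 7 × ICC)/80], where 7 is the group size minus one. This is 1.897 at ICC 0, 1.750 at ICC 0.05 and 1.633 at ICC 0.10. At ICC 0, power per outcome is 0.249 at 0.01 and 0.274 at 0.0125.

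The chance that at least two of four succeed, with 0.3 SD on all four outcomes, by simulation:

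| ICC | r | 0.01 | 0.0125 | Holm |
|---|---|---|---|---|
| 0 | 0 | 0.259 | 0.302 | 0.361 |
| 0 | 0.6 | 0.285 | 0.316 | 0.356 |
| 0.05 | 0.2 | 0.209 | 0.243 | 0.289 |
| 0.10 | 0 | 0.141 | 0.171 | 0.214 |
| 0.10 | 0.6 | 0.191 | 0.216 | 0.250 |

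Over the whole assumed range, moving from 0.01 to 0.0125 adds 2.5 to 4.3 points. Holm adds a further 3.4 to 5.9 points over 0.0125.

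**5. Error control under Holm.** Ordered p-values are compared with 0.05/4 = 0.0125, 0.05/3 = 0.0167, 0.05/2 = 0.025 and 0.05. Familywise error stays at or below 0.05 under any dependence. A false two-of-four claim requires at least one false rejection, so its chance is also at most 0.05.

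**The case against.** The best defence is that 0.01 is simply 0.0125 rounded, and that it errs on the strict side. Either reading keeps familywise error at or below 0.05, so no false-positive claim becomes easier, and the power difference is only a few points. All of that stands, and it limits the finding to an inconsistent threshold; there is no failure of error control. It does not say which number decides when p falls between them.

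A reader might also infer that Bonferroni is the wrong method here and wastes error rate. The article does not support that. It uses the threshold to test each of the four outcomes, and Bonferroni is valid for that purpose. Holm is more powerful, but preferring it is a matter of efficiency. The 0.04 obtained from four tests at 0.01 is the rate of any false positive; it is not the error rate of the two-of-four claim, which is bounded by 0.030 at 0.01 and 0.0375 at 0.0125.

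Nor should the low absolute power in the table be blamed on this threshold. Sizing the trial "with a statistical power of 0.8 and a significance level of .05", while testing at a smaller alpha, is a separate matter. Even under Holm, power at 0.3 SD stays below 37% throughout the assumed range.

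**Conclusion.** The point holds as an internal contradiction in the primary decision rule. The figure and the formula differ by 0.0025, and any primary outcome with p in that interval gets opposite verdicts. If it is the second outcome, the primary hypothesis changes with it. Type I error is not inflated under either reading. The cost of the stricter figure is about 2.5 to 4.3 points of two-of-four power, given 80 analysed per arm, 0.3 SD on all four outcomes, and the assumed ICC and correlation ranges. The contradiction itself is arithmetic and rests on none of those assumptions. It has to be corrected because it concerns the rule that decides the trial, although its numerical effect is small.

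**What to change.** Before outcome data are seen, replace the printed threshold with one exact value, 0.0125 (two-sided, 0.05/4), and state that the primary hypothesis is met when at least two of the four outcomes pass it in favour of ACT. This costs one sentence; error control is unaffected.

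Optionally, and not as a correction, name Holm's step-down procedure with thresholds 0.0125, 0.0167, 0.025 and 0.05, and declare the primary hypothesis met when at least two outcomes are rejected. It rejects everything that Bonferroni at 0.0125 rejects, keeps both the familywise error and the worst-case two-of-four error at or below 0.05, and adds about 5 points of two-of-four power at 0.3 SD (3.4 to 5.9 over the assumed range). Because it is more permissive than the published threshold, it should be adopted only if the change is documented before outcome data are seen.

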## Discussion

As shown by large epidemiological studies [76,77] cardiovascular risk can be described as multi-factorial and preventable because a greater percentage of the overall risk is comprised of modifiable risk factors [1-3]. Unhealthy life-styles, poor medication adherence, and psychological distress affect the prognosis of cardiac patients. ACT has proven efficacious at promoting and maintaining life-style changes and improving quality of life. Thus, it appears to be a promising method to improve quality of life and disease progression.

However there is a paucity of research examining treatment effects of ACT in the context of secondary prevention of IHD. Conducted in a clinical context, the ACTonHEART study will assess whether an ACT-based intervention (compared to usual care) can improve psychological health, and adherence to medical and behavioral regimens among a sample of patients diagnosed with IHD. ACTonHEART is developed in such a way that multiple risk behaviors are targeted at once. Although modification of each separate risk factor adds considerably to the standard care of cardiovascular patients, the majority of these patients have more than one risk factor. The compounded effects of multiple risk factors can be efficiently and effectively addressed with comprehensive interventions.

The ACTonHEART study is innovative in a number of ways. First, although ACT is becoming well-studied in the traditional clinical context, large-scale application to medical settings has not occurred. Second, the assessment framework incorporates indicators of both physical and psychosocial health. The inclusion of objective physiological outcome measures constitutes an aspect of innovation in ACT research. Last, the study will focus on mediation mechanisms underlying treatment success and presents possible links to systematic models on psychological flexibility, a key construct in ACT research.

Some aspects of the study design can limit recruitment and retention of participants. For example, the inclusion criterion of having an INTERHEART Modifiable Risk Score > 9 may slow recruitment. However, it is believed that floor effects and subsequent underestimation of treatment effects can be reduced by targeting individuals with adherence difficulties [78].

Among the major strengths of this study is the novelty of utilizing ACT to modify multiple cardiac risk factors with a brief intervention. This study is consistent with the call for prevention and health promotion research integrating psychosocial (e.g., depression) and behavioral (e.g., physical activity) risk factors [79]. Moreover, the inclusion of an EU standardized-care condition will provide important information pertaining to the added benefits of an ACT-based intervention and reduce inflation of treatment effects.

Another methodological strength of the study is the use of a multi-level model accounting for intraclass correlation due to clustering of patients in small therapy groups. Although several studies focuses on group therapy interventions, very few take control for this additional source of variance, potentially leading to significant bias.

This trial will be redacted following the CONSORT guidelines for non-pharmacological trials [80], and outcomes published in peer-reviewed clinical journals.

## Conclusions

To the best of the researcher’s knowledge, this study will be the first randomized controlled trial to examine the effectiveness of ACT to improve adherence to medical and behavioral prescription among cardiac patients. Conducted in the context of clinical practice, this trial will potentially offer empirical support to alternative interventions to improve quality of life and reduce mortality and morbidity rates among cardiac patients. Moreover, by virtue of its short duration, the program could potentially be utilized for health promotion and the primary prevention of CVD.

## Abbreviations

ACT: Acceptance and Commitment Therapy; ACTonHEART: Acceptance and Commitment Therapy on heart patients; IHD: Ischemic heart disease; CR: Cardiac rehabilitation; LDL: Low density lipoprotein; HDL: High-density lipoprotein; BMI: Body mass index; PGWB: Psychological General Well-Being.
